## Abstract

**Background:**

Suicide is the leading cause of death among young Australians, accounting for one-third of all deaths in those under 25. Schools are a logical setting for youth suicide prevention activities, with universal, selective and indicated approaches all demonstrating efficacy. Given that international best practice recommends suicide prevention programmes combine these approaches, and that to date this has not been done in school settings, this study aims to evaluate a suicide prevention programme incorporating universal, selective and indicated components in schools.

**Methods:**

This study is a trial of a multimodal suicide prevention programme for young people. The programme involves delivering universal psychoeducation (safeTALK) to all students, screening them for suicide risk, and delivering internet-based Cognitive Behavioural Therapy (Reframe IT) to those students identified as being at high risk for suicide. The programme will be trialled in secondary schools in Melbourne, Australia, and target year 10 students (15 and 16 year-olds). safeTALK and screening will be evaluated using a single group pre-test/post-test case series, and Reframe IT will be evaluated in a Randomised Controlled Trial. The primary outcome is change in suicidal ideation; other outcomes include help-seeking behaviour and intentions, and suicide knowledge and stigma. The programme’s cost-effectiveness will also be evaluated.

**Discussion:**

This study is the first to evaluate a suicide prevention programme comprising universal, selective and indicated components in Australian schools. If the programme is found to be efficacious and cost-effective, it could be more widely disseminated in schools and may ultimately lead to reduced rates of suicide and suicidal behaviour in school students across the region.

**Supplementary Information:**

The online version contains supplementary material available at 10.1186/s13063-022-06072-8.

## Background

Suicide is the leading cause of death in young Australians, accounting for more than one-third of all deaths in those under 25 [1]. Suicidal ideation and behaviour, including non-fatal suicide attempts and self-harm, are more common and are associated with a host of negative outcomes including risk of future suicidal behaviour and suicide [2, 3]. The impact of suicide on a young person’s family, friends, and wider community can be devastating and may include increased risk of suicidal behaviour and suicide [4]. There is therefore an urgent need to develop and test acceptable and accessible approaches to preventing suicide and suicidal behaviours in this population.

Schools are an appropriate and convenient setting for the delivery of youth suicide prevention programmes [5] and have been identified as important locations for suicide prevention activities by national and international suicide prevention strategies [6, 7]. Although school wellbeing staff may be well-placed to provide support to students at risk of suicide, young people are often reluctant to seek help from professionals and instead turn to their friends for support [8]. School-based prevention efforts must therefore not only target school staff, but also fellow students. Historically, there has been a reluctance to deliver suicide prevention efforts to students, due to concerns about the potentially iatrogenic impact of asking or talking about suicide [9, 10]. However, increasing evidence suggests that it is safe to do [11–13]. Moreover, a recent systematic review and meta-analysis [14] revealed that school-based suicide prevention programmes should combine universal, selective, and indicated approaches in order to be most effective. Each approach as it relates to school settings is reviewed briefly below.

### Universal approaches

Universal approaches target whole populations, regardless of risk [15]. In school settings, these typically involve psychoeducation programmes, which aim to increase suicide literacy and reduce stigma, encourage help-seeking, and equip participants with skills to support peers [16]. A number of psychoeducation suicide prevention programmes have been tested internationally and appear to increase knowledge, attitudes, and help-seeking intentions; some have also been associated with reductions in suicidal ideation and behaviour [17–21]. One example is LivingWorks safeTALK, a 3.5-h workshop suitable for delivery to anyone over the age of 15. The programme has been positively evaluated in adult populations [22–25]. In 2015, our team conducted a pilot evaluation of safeTALK in secondary schools in Alice Springs, Australia, with 129 students (mean age = 16.7 years). The intervention was associated with increased knowledge about suicide, confidence to intervene with a suicidal person, and willingness to seek help and help others. No iatrogenic effects were reported [26].

### Selective approaches

Selective approaches aim to prevent the onset of suicidal thoughts or behaviour in populations at elevated risk of suicide [27]. In school settings, these include training gatekeepers, such as teachers, to recognise and intervene with students at risk, and screening students for suicide risk followed by referral to relevant support. Screening can facilitate the identification of at-risk students, including those who have not previously sought help, and has not been associated with iatrogenic effects [28–30]. As part of the evaluation of safeTALK described above, screening questions were embedded into the questionnaires to identify students potentially at risk of suicide. Almost half of the participants screened positive, many of whom had not previously sought help, and were referred for further support [26].

### Indicated approaches

Indicated approaches target those individuals already displaying suicidal thoughts and/or behaviours and include face-to-face psychotherapy, pharmacotherapy, and more recently, online programmes. A range of online programmes targeting suicidal thoughts have been developed and evaluated, with promising results [31, 32]. The “Reframe IT” programme was developed by our team in 2011. Reframe IT is an online cognitive behavioural therapy (CBT) programme specifically designed for young people presenting to the school counsellor with suicide risk. Reframe IT was piloted in two phases. First, a pre-test post-test case series study found it to be associated with reduced suicidal ideation, depression, and hopelessness [33]. Second, in a pilot randomised controlled trial, the intervention group showed larger (non-significant) mean improvements in suicidal ideation, depression, and hopelessness, when compared to controls [34]. Participants in both studies provided positive feedback about Reframe IT, and it was not associated with any iatrogenic effects [33–35].

### Integrated approaches to suicide prevention

According to international best practice, suicide prevention programmes should incorporate universal, selective, and indicated approaches [15]. Such approaches have shown promise in both community and school settings, although the majority of those in school settings combine only two levels of prevention, such as universal (e.g. psychoeducation) and selective (e.g. screening) components [14]. There is therefore a need to develop, implement, and evaluate an approach combining universal, selective, and indicated approaches in school settings. To enable ongoing implementation and dissemination of such a programme, evidence must support not only its efficacy but also its cost-effectiveness. To date, no studies (Australian or otherwise) have applied rigorous economic methodology to evaluate short- and longer-term comparative cost-effectiveness of an intervention comprising universal, selective, and indicated elements.

### Aims and hypotheses

This project aims to evaluate the effectiveness of an integrated programme comprising universal, selective, and indicated components in reducing suicide risk, improving risk recognition, and increasing health service use among young people across North West Melbourne. Secondary aims are to evaluate the programme’s safety and cost-effectiveness. The programme involves the delivery and evaluation of universal educational workshops (safeTALK) to school students plus screening students for suicide risk (universal and selective approaches; Component 1), and the evaluation of online CBT (Reframe IT) delivered to students identified as being at risk (indicated approach; Component 2). Several hypotheses have been generated relating to each of the project components as well as the project as a whole.

It is hypothesised that completion of the safeTALK workshop will be associated with increased intentions to intervene with a suicidal person, higher levels of suicide literacy, higher levels of perceived behavioural control regarding intervening with a suicidal person, and reduced stigma towards suicide and suicidal behaviour.

It is hypothesised that the screening will lead to the identification of students at risk of suicide-related behaviour who had not previously sought help.

It is hypothesised that, compared to the control group, students in the Reframe IT intervention group will demonstrate reduced suicidal ideation, reduced symptoms of depression, reduced hopelessness, and improved problem-solving.

It is hypothesised that the project as a whole will lead to increased health-service use; increased help-seeking from informal sources; and improved attitudes towards help-seeking.

Finally, it is hypothesised that the programme will be cost-effective and have no iatrogenic effects.

## Methods

### Study design

The present study will adopt two methodological approaches: Component 1 will employ a single-group, pre-test/post-test case series; Component 2 is a parallel superiority randomised controlled design, where the intervention condition (Reframe IT plus treatment as usual; TAU) is compared to TAU. Component 2 will be conducted and reported according to the Consolidated Standards of Reporting Trials (CONSORT) statement [36].

The study was designed to be conducted over a 5-year period (2019–2023), with a 3-year intervention phase. There has, however, been a 1-year suspension due to the COVID-19 pandemic during 2020, meaning that the study will continue into 2024.

The study is registered with the Australian New Zealand Clinical Trials Registry (ID: ACTRN12621000770864). This is the primary registry of the WHO ICTRP network. It includes all items from the WHO Trial Registration data set, available at https://www.anzctr.org.au/Trial/Registration/TrialReview.aspx?id=381921&isClinicalTrial=False. It received ethical approval from the University of Melbourne Human Research Ethics Committee (HREC; ID 1852317) and the Department of Education Victoria Research Ethics Committee (ID 2019_003951) [see Additional files 2 and 3].

This protocol is reported in line with the Standard Protocol Items: Recommendations for Interventional Trials (SPIRIT) 2013 statement [37, 38] [see Additional file 4 for checklist].

### Setting

This study is led by researchers at Orygen in Melbourne, Australia. Orygen is a youth mental health organisation with expertise in research, policy, education, and innovations in care. Since 1984, Orygen has been working side-by-side with young people to reduce the impact that mental ill-health has on young people, their families and society. Orygen services the north and west metropolitan areas of Melbourne, which, with a population of approximately 1.67 million, is one of the fastest growth corridors in Australia [39, 40]. It includes 31% of the state’s total population [40] and 11 of Melbourne’s 14 most disadvantaged municipalities, and reports high levels of mental illness [39, 40].

Orygen research staff are part of the Centre for Youth Mental Health, University of Melbourne. This project is a partnership with Lifeline Australia and the Department of Education and Training Victoria. Other collaborators are the University of Melbourne School of Population and Global Health, Deakin University, and the University of Auckland.

The catchment area for the current study aligns with the four geographical areas that comprise north and west metropolitan Melbourne, according to the regional model operated by the Department of Education and Training Victoria and the Department of Health and Human Services Victoria as well as Orygen’s clinical catchment area [41, 42]. Mainstream secondary schools that are located in the study catchment area and have year 10 students enrolled will be eligible as study sites; at the time of publication, 141 schools meet these criteria. A list of participating schools will be maintained.

### Participants

Participants will primarily be consenting year 10 students (i.e. aged 15–16) from secondary schools in north and west Melbourne. Year 11 students will also be included if the school perceives a strong need for delivery of the programme to this year level, or if we struggle to meet the required sample size (see section “Sample size and power calculation” of this paper). Exclusion criteria are intellectual disability and inability to converse in or read English. The additional inclusion criterion for participation in Component 2 (Reframe IT randomised controlled trial) is past 4-week suicidal ideation, as indicated by either a score of 21 or higher on the Suicidal Ideation Attributes Scale (SIDAS), or a score of 1–20 confirmed by a screening interview with a researcher.

#### Plans to promote participant retention and complete follow-up

Each participating school will be invited to nominate key staff members to complete Applied Suicide Intervention Skills Training (ASIST), delivered free-of-charge by Lifeline facilitators, to increase staff capacity to enact safety protocols. We hope this will also act as an incentive for schools to participate. The study team will take all reasonable steps to minimise any potential burden on school staff. Periodic communications will be provided to school leadership via newsletters and presentations to update on the progress of the study, and to acknowledge their support. Upon completion of the study, schools will also be provided with an anonymised aggregate report of the questionnaire data collected.

### Discontinuation and withdrawal

Participants who are withdrawn or discontinued from the study will not be replaced.

#### Voluntary discontinuation

Participants are free to discontinue their participation at any time. Participants who discontinue from the study will always be asked about the reason(s) for their discontinuation and about the presence of any adverse events. All adverse events will be followed up until resolution or the participant is lost to follow-up.

#### Participant discontinuation criteria

A participant will be considered discontinued from Component 1 if they do not attend the safeTALK workshop for any reason (including if they leave the workshop in the first 30 min). Participants who arrive more than 30 min late to the safeTALK workshop will miss important safety and wellbeing information, and will not be permitted to continue; they will also be considered discontinued from Component 1. Given that some students in Component 1 will also be participating in Component 2, all students regardless of their safeTALK completion will be asked to complete the subsequent questionnaires.

If a participant leaves the workshop early, a member of the study team will record how much of the workshop they completed and use this to determine whether the participant is considered “withdrawn”.

A participant will be discontinued from the study if they miss the T1 assessment. If a student consents but misses the baseline assessment, they may complete the baseline any time prior to T2, after which they will be discontinued.

A participant allocated to the intervention group in component 2 will be discontinued if:
Use of the intervention interferes with appropriate clinical management of risk of harm to self or others (as judged by the school wellbeing staff and/or senior researchers);Serious adverse events (SAEs; defined in section “Definitions of adverse events and serious adverse events”) occur that could be associated with the Reframe IT intervention;The participant or their parent or guardian indicates they no longer wish to use the Reframe IT intervention.

#### Participant withdrawal criteria

A participant will be considered “withdrawn” from the study in cases where all involvement is ceased.

A participant will be withdrawn if:
Participation interferes with appropriate clinical management of risk of harm to self or others (as judged by the school wellbeing staff and/or senior researchers, and in consultation with treating clinicians if appropriate);SAEs occur that could be associated with any intervention included in this study;The participant or their parent or guardian indicates they no longer wish to participate;The participant leaves the school.

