### Statistical analyses

#### Component 1

For each continuous outcome, changes over time will be assessed using linear mixed effects modelling with school included as a random factor. This analysis will examine whether there is a trend over time and whether the trend is linear or non-linear. Change in current suicidal ideation between T1 and T2 will be assessed using the McNemar–Bowker symmetry test for nominal data.

#### Component 2

Descriptive statistics will be used to compare participant characteristics between the study arms, and to assess for any imbalance.

The analysis will adopt the intention-to-treat approach, which is to include in the analysis all participants who have been randomised and regard each participant as belonging to the randomised group concerned irrespective of protocol adherence. Difference in change in the primary outcome of SIDAS score between the treatment groups will be examined using linear mixed effects modelling with the treatment group as a fixed factor and school included as a random factor. Secondary outcome measures will be similarly analysed. As a secondary analysis, compliance (as measured by the number of modules completed) and other potential covariates (e.g. gender) will be accounted for.

If the amount of missing data is non-trivial, multiple imputation will be considered to handle the missing data.

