##### Serious adverse event (SAE)

An SAE is any untoward medical occurrence that:
Results in death;Is life-threatening;
Life-threatening in the definition of serious refers to an event in which the participant was at risk of death at the time of the event; it does not refer to an event which hypothetically might have caused death if it were more severe.Requires inpatient hospitalisation or prolongation of existing hospitalisation;Results in persistent or significant disability/incapacity;Is a congenital anomaly/birth defect;Is an important medical event that although not immediately life-threatening or result in death or hospitalisation, based upon appropriate medical and scientific judgement, may jeopardise the participant and/or require intervention to prevent one of the outcomes listed above.

Outpatient treatment in an emergency department is not in itself an SAE, although the reasons for it may be (e.g. suicide attempt).

Hospital admissions and/or surgical procedures planned before or during a study are not considered SAEs if the illness or disease existed (or the surgery was planned) before the participant was enrolled in the study, provided that it did not deteriorate in an unexpected way during the study.

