#### Assessment and documentation of AEs

All AEs and SAEs that arise during the trial will be recorded in the study database. The causality of AEs and SAEs (i.e. their relationship to intervention treatment) will be assessed by a suitably qualified study team member. Where possible, information related to causality will be collected from the participant who experienced the adverse event (i.e. whether or not the participant themselves attributes the AE to the intervention) as well as any relevant collateral information from family members, friends, and school staff. Any AE that is serious (i.e. life-threatening) will be reported to the Sponsor and to the relevant ethics committees within 24 hours of the research team becoming aware of its occurrence, regardless of the relationship to the intervention.

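### One SAE makes a Reframe IT student both discontinued and withdrawn with all involvement ceased, so T3/T4 outcome data may be lost, possibly unequally between arms, despite the intention-to-treat commitment

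*Protocol article*

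**What the plan says.** Participant discontinuation criteria: "A participant allocated to the intervention group in component 2 will be discontinued if" one of three conditions is met. One is that SAEs "occur that could be associated with the Reframe IT intervention". Another is that the participant or guardian "indicates they no longer wish to use the Reframe IT intervention".

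Participant withdrawal criteria: a participant counts as withdrawn "from the study in cases where all involvement is ceased". Withdrawal is mandatory if, among other things, "SAEs occur that could be associated with any intervention included in this study".

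Statistical analyses, Component 2: the intention-to-treat approach is to "include in the analysis all participants who have been randomised", whatever their adherence. Multiple imputation will only be considered, and only if missing data are non-trivial. The primary outcome is change in SIDAS from T2 to T3 and T4.

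Three other sections bear on this. Study discontinuation criteria names safeTALK, screening and Reframe IT as the interventional components. Randomisation and treatment allocation says that only the statistician is blind. Assessment and documentation of AEs gives the causality judgement to a study team member.

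On reporting, Assessment and documentation of AEs says: "Any AE that is serious (i.e. life-threatening) will be reported to the Sponsor" and the ethics committees within 24 hours. The SAE definition is wider and includes an event that "Requires inpatient hospitalisation or prolongation of existing hospitalisation".

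**The concern.** The two SAE criteria give one event two statuses with different consequences for data. The text does not tell a site whether a Reframe IT student with such an SAE should still be asked for T3 and T4 questionnaires. Read literally, the withdrawal rule answers no.

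The outcome data at stake come from students selected for suicidal ideation who then had a serious event, so the gaps are unlikely to be missing at random. The trigger is also not symmetric. A control student can meet it through safeTALK or screening. A Reframe IT student can meet it through either of those or through Reframe IT. The test is a low one (could be associated), and people who know the allocation apply it. If the students removed have worse change than those who stay, the comparison shifts in favour of Reframe IT.

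Separately, the gloss on serious in the 24-hour reporting sentence is narrower than the protocol's own SAE definition.

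**Working it through.** **The two rules side by side**

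- Discontinued: Reframe IT arm only; the SAE could be associated with Reframe IT. The neighbouring criteria concern use of the intervention.
- Withdrawn: any participant; the SAE could be associated with any study intervention; all involvement ends.
- Reframe IT is a study intervention, so the first trigger is a subset of the second. For SAEs the lesser status never operates alone.
- For Component 1 the article says that students keep completing questionnaires whether or not they completed safeTALK. It has no matching sentence for a Component 2 student who is discontinued. That such a student stays in follow-up is inferred from the separate status and its wording.

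**The plan's own figures**

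- Loss allowance: 268 / (1 − 0.20) = 335 randomised, as stated; 335 / 2 = 167.5 per arm.
- Planned difference: 61.6 − 47.1 = 14.5 SIQ points. It is used here only as a yardstick of size.
- Sample size: with SD 42.3, two-sided 5% and 80% power, 2 × (42.3 × (1.960 + 0.842) / 14.5)² ≈ 133.6, so 134 per arm. This matches the stated figure without the design effect of 1.1.

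**Bias from the loss**

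Inputs from the article: SDs of change 42.3 and 41.6, so pooled SD = √((42.3² + 41.6²) / 2) = 41.95.

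Assumed, because the article gives no SAE rates: withdrawal proportions p₁ (Reframe IT) and p₀ (control), and removed students' unseen change k SD worse than that of students who stay, with k the same in both arms.

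If a proportion p is unseen and k SD worse, the observed arm mean is too favourable by p × k × SD. The bias in the difference is therefore k × SD × (p₁ − p₀).

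| Assumed p₁ vs p₀ | Students lost (of 167.5 per arm) | Bias, k = 1 (share of 14.5) | Bias, k = 2 (share of 14.5) |
|---|---|---|---|
| 1% vs 0.5% | 1.7 vs 0.8 | 0.21 (1.4%) | 0.42 (2.9%) |
| 3% vs 1% | 5.0 vs 1.7 | 0.84 (5.8%) | 1.68 (11.6%) |
| 5% vs 1% | 8.4 vs 1.7 | 1.68 (11.6%) | 3.36 (23.1%) |
| 5% vs 5% | 8.4 vs 8.4 | 0 | 0 |

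Example: 2 × 41.95 × (0.05 − 0.01) = 3.36, and 3.36 / 14.5 = 23.1%.

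Effect on false claims of benefit with 134 analysed per arm: SE = 41.95 × √(2/134) = 5.13, ignoring clustering. With no true effect, the chance of a significant result favouring Reframe IT is 1 − Φ(1.96 − bias/SE). It is 2.5% without bias, 2.8% to 3.0% at 1% vs 0.5%, and 5.1% to 9.6% at 5% vs 1%.

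**Reporting wording**

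An inpatient admission that was not life-threatening is an SAE under the definition. Under the gloss in the reporting sentence it falls outside the 24-hour duty. Both cannot be meant.

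**The case against.** Much can be said for the plan, and most of it limits the size of the problem without removing the conflict.

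- **Safety data.** A reader might infer that withdrawal hides harms. The documents do not support this. All AEs and SAEs are to be recorded in the study database, and serious events are reported regardless of relationship to the intervention. Voluntary discontinuation adds that all AEs are followed to resolution or loss to follow-up. What is lost is later self-report.
- **Clinical-risk criteria.** A reader might infer that these conflict too. They do not: one concerns use of the intervention, the other participation. The criteria on the participant's wishes are tiered in the same way. Only the SAE criteria lack the distinction.
- **Intention-to-treat.** The analysis section is not contradicted in wording. A mixed model can keep earlier scores, imputation is foreseen, 20% drop-out is allowed for, and an SAE after T3 costs only T4. This stands, but none of it makes a loss triggered by an SAE ignorable.
- **Size.** Five percent of an arm is about eight students with attributable SAEs, while the Background reports no iatrogenic effects in either Reframe IT pilot study. Controls can also be withdrawn. It would be wrong to pick one scenario, such as no control removals and a gap in score level instead of change from T2, and quote its bias as the finding.
- **School leavers.** A reader might extend the point to students who change school and suggest sending them the online questionnaire. But assessments run in class at school, and the school holds ongoing risk management, so the article does not support this as a simple remedy.

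**Conclusion.** The point holds as a conflict in the text with a possible, unquantified bias. The SAE criteria for discontinuation and withdrawal overlap completely for events linked to Reframe IT, and the stronger status ends outcome collection in randomised students, which undercuts the intention-to-treat commitment in effect.

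That the loss may be greater in the Reframe IT arm is a structural inference from the extra exposure and the unblinded causality judgement; the article gives no rates to confirm it. The direction, in favour of Reframe IT, holds only if removed students do worse and more of them come from that arm. The illustrated range, about 1% to 23% of 14.5 points, rests on the assumed rates, on a deficit of 1 to 2 SD in change, and on neither the mixed model nor imputation recovering it. At rates near 1% the effect is small, and at equal rates it is nil.

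The mismatch between the reporting gloss and the SAE definition is a separate drafting error. It does not add to the bias argument. Both are worth correcting because the loss is set by the protocol's own wording and the correction is cheap.

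**What to change.** 1. Reconcile the SAE criteria in Participant discontinuation criteria and Participant withdrawal criteria with the Component 2 analysis section, so that stopping an intervention after an SAE is distinguished from stopping outcome collection. Which clinical criteria apply, and when, is for the investigators.
2. State that T3 and T4 assessments are still sought from randomised students after such an SAE where the participant and guardian agree and those responsible for clinical risk do not judge participation itself to interfere. Say explicitly whether a discontinued Component 2 student stays in follow-up.
3. Reconcile the gloss on serious in the 24-hour reporting sentence with the full SAE definition.

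Cost: a protocol amendment notified to or approved by the ethics committee, possibly a matching change to the consent form, and a small number of extra questionnaires. The sample size does not change.
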